| **Primary registry and trial identifying number** Pan African Clinical Trial Registry  PACTR202109586388973  **Date of registration in primary registry** 28 September, 2021  **Secondary identifying numbers/Acronym** I-decide  **Source(s) of monetary or material support:** The PI ([name])  **Primary sponsor**: The PI  **Secondary sponsor(s)**: None  **Contact for public queries**: [name], BScN, MScN [[name]] [[contact]]  **Contact for scientific queries**: [name], BScN, MScN [[name]] [[contact]]  **Public title**: Effectiveness of targeted antenatal family planning information provision on early postpartum family planning uptake in Kisumu county  **Scientific title:** Targeted Antenatal Information Provision and Postpartum Fertility Decisions  **Countries of recruitment**: Kenya  **Health condition(s) or problem(s) studied**: Female Fertility, Contraceptives  **Intervention(s)**  **Active comparator:** Antenatal provision of Postpartum Family Planning (PPFP) Information and appointment setting for 14 weeks postpartum follow-up  **Control comparator:** Routine Antenatal care  **Key inclusion and exclusion criteria** The study will be conducted in 4 primary health centres and 2 communities in the Kisumu East sub-county. The Health centres are eligible if : They offer the continuum of ANC, delivery, and PNC; They provide a selection of at least three modern contraceptive methods that are rated 2 or 1 on the Medical Eligibility Criteria (MEC) for Postpartum Contraceptives and referrals for other methods to clients; There were no stock-outs of contraceptives during the preceding six months; They have on average at least 10 deliveries per month; and They are willing to participate.  All pregnant women will be eligible to participate in the study if: They are in their second pregnancy trimester; The woman is attending ANC and has intention of attending PNC at the health centre; An informed consent is obtained; and Resides within 20km  Excluded from the study will be clients: in similar study; with latex sensitivity; not anticipating a male partner in the next 12 months; unable to complete consent form as determined by the study nurse or cha and whose only male partner has had a vasectomy.  **Study type** Interventional  **Allocation:** randomized  **Intervention model:** concurrent assignment  **Masking:** None  **Primary purpose:** prevention  Phase II  **Date of first enrolment** Nov 2021  **Target sample size** 246  **Recruitment status** Not Recruiting  **Primary outcome(s)** Nature of Fertility decisions postpartum. Primarily the uptake of immediate postpartum FP being the main outcome – 14 weeks postpartum  **Key secondary outcomes** Fertility intentions. Primarily whether they accept to book an appointment for postpartum family planning - 14 weeks postpartum  Knowledge of family planning methods – Any time after intervention |

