| The study core team will have a coordinating centre in Gita Sub county Hospital. The steering committee will be composed of the PI and the 3 CoPIs.  The steering committee has the oversight of Trial title, sourcing for funding, protocol amendment, follow-up on data collection and management recommendations by data management team, setting recruitment date, setting recruitment end date, monitoring actual recruitment rate versus the projected recruitment rate, consenting process, summarising protocol deviations, site visits and site reporting of organizational problems or other trial issues  Data management team will comprise the PI, Data Clerks at the sites and the study nurse and Community Health Worker: set acceptance rate proportion (those who accepted to participate versus those sampled), monitoring retention (percentage of participants proceeding from recruitment, treatment to follow-up including missing outcome data), monthly forecast of recruitment for the trial period remaining, monitoring loss to follow-up as a proportion of the ones not yet reached by 16 weeks postpartum follow-up to those who were recruited, overseeing data management metrics i.e. rate of electronic data capture, return dates and rate of returns, number of completed follow-up, withdrawal rate, monitoring intervention fidelity by the study nurse or Community Health Worker (CHW), Data quality checks, results dashboard review  The end point adjudication team will comprise the PI, the facility in-charges of the study facilities, the sub-county RH coordinator. |
| **Introduction** | |

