| Outcomes (12) | Primary Outcome  Nature of Fertility decisions postpartum. Primarily the uptake of immediate postpartum FP being the main outcome. To be measured at or after 14 weeks postpartum. It is a proportion.  Secondary Outcome  1. Fertility intentions. Primarily whether they accept to book an appointment for postpartum family planning. Will be assessed soon after the intervention has been administered. It will be a proportion of those intending to use PPFP versus those who participated.  2. Knowledge of family planning methods. Will be assessed soon after the intervention has been administered or recruitment (for controls). It will be a proportion of level of knowledge on PPFP among participated.  3. Uptake of postnatal services. Will be measured at 14 weeks postpartum and it will be a proportion of utilization of postnatal services among participants.  4. Perceived control of fertility decision. Will be a proportion among participants. To be measured soon after intervention or recruitment (for the controls)  5. Attitude toward PPFP Will be a proportion among participants. To be measured soon after intervention or recruitment (for the controls)  No harm outcomes are premeditated |
| Participant timeline (13) | This being a behavioural intervention, the recruitment and interventions will be done simultaneously.  Client exit interviews will be done immediately or soonest possible time after the intervention  Questionnaire will be administered at or soon after 14 weeks postpartum.  (see annexes 1 and 2)  [figure not shown] |

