| Recruitment (15) | Each health centre and community unit will have a trained research assistant. The assistant is to ensure adherence to the study manual and standard operating procedures for data management. The primary outcomes will largely be assessed based on the CRFs, appointment card and questionnaire. Actual uptake of modern contraceptive method will be established three months postpartum between the 12th to 14th weeks after birth. The CRFs will be filled on recruitment by the trained ANC service provider. The appointment card will be filled by the health worker after the client has accepted to set postnatal follow up date for PPFP. The questionnaire will be filled at 14 weeks postpartum during the scheduled MCH visit by a trained enumerator.  The client exit interview guide and site visit appraisal form will be used to assess the process indicators. Client exit interviews will be done by trained enumerator on the earliest opportunity after the intervention has been administered to reduce recall bias by the client. Site appraisal form will be filled on site visits by the research team and on the part of enumerator will be filled each day to include workload for ANC, number of staff available to offer ANC services, availability of FP counselling bag and flipchart. Lose to follow-up will be called to find the status of the client |
| **Methods: Assignment of interventions (for controlled trials)** | |
| Allocation: |  |
| Sequence generation (16a) | Each client meeting the criteria will be randomly assigned to the study i.e. to the intervention and to the control arms using simple random sampling by picking folded paper labelled “yes” or “no”. There will be no blinding as the intervention facilities and controls are known and will be separate to reduce contamination. |
| Allocation concealment mechanism (16b) | There will be no allocation concealment as the intervention and control facilities are known and separate to reduce contamination. |
| Implementation (16c) | The allocation to intervention and control is at the facility level. The participants will be enrolled by the study nurse for both the community and facility arms. Participants will be assigned to participate by picking a ballot paper labelled “yes” or “no” enclosed in resembling envelopes |
| Blinding (masking) (17a,b) | None of the implementers and participants will be blinded thud there equally no plan for controlled unblinding. |

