| Protocol amendments (25) | Plans for communicating important protocol modifications (eg, changes to eligibility criteria, outcomes, analyses) to relevant parties (eg, investigators, REC/IRBs, trial participants, trial registries, journals, regulators)  Protocol amendments will be communicated by the PI to the Pan-African Clinical Trials Registry (PACTR), British Medical Journal (BMJ) (Journal for Trials), MMUST Institutional Ethics Review Committee (IERC) and NACOSTI |
| Consent or assent (26a,b) | The trials nurse at each site will obtain the consent from the trial participants |
| There will be no need for additional consent provisions to use individual participant’s data and biological specimens as the study will not publish individual participant data but anonymous group data and there are no biological specimen being collected. |
| Confidentiality (27) | Personal information about potential and enrolled participants will be collected using kobo tool box and submitted by the study nurse or CHW to the study server. Individual participants will be allocated randomly generated enrolment numbers to maintain anonymity all through the trial period. Access to data will be password encrypted. |
| Declaration of interests (28) | GG is the Chief officer of Health in Kisumu County but is not directly involved in care provision of the essential services to the study participant. The county government of Kisumu nurses employed in the facilities and the Community Health Assistants (CHA) will be the implementers of the intervention. All other core team members declare that they have no conflict of interest. |
| Access to data (29) | Access to trial dataset will be controlled. Request to be done by email to the principal investigator The decision is by the Research team lead by the Principal investigator. Criteria for reviewing the request: Qualification of the person requesting, description of the purpose of the request, willingness to engage the Principal investigator in the development of analysis plan, and monographs or manuscripts. |
| Ancillary and post-trial care (30) | No harm is anticipated in this trial thus no defined ancillary and post trail compensation. |

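### The endpoint adjudicators are trial and site staff with no stated masking, and uptake at 14 weeks has no stated check against a service record

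*Protocol*

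**What the plan says.** The section on roles and committees, just before the Introduction, states: "The end point adjudication team will comprise the PI, the facility in-charges of the study facilities, the sub-county RH coordinator". It does not say which records the team sees or how a woman is to be classified as a user. The registration summary lists masking as none and gives "Primary sponsor: The PI"; the principal investigator (PI) is also the source of funding. The PI sits on the steering and data management teams as well.

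On knowledge of arm:
- Sequence generation (16a): "There will be no blinding as the intervention facilities and controls are known and will be separate to reduce contamination".
- Implementation (16c): "The allocation to intervention and control is at the facility level".
- Blinding (17a,b): "None of the implementers and participants will be blinded".

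On the endpoint, Outcomes (12) says: "Primarily the uptake of immediate postpartum FP being the main outcome. To be measured at or after 14 weeks postpartum. It is a proportion". Recruitment (15) and Data collection methods (18a,b) say it will be assessed, 'largely', from the CRF, the appointment card and the questionnaire. On the last of these: "The questionnaire will be filled at 14 weeks postpartum during the scheduled MCH visit by a trained enumerator". Women who are lost to follow-up are telephoned.

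Confidentiality (27) adds: "Individual participants will be allocated randomly generated enrolment numbers to maintain anonymity all through the trial period".

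**The concern.** Women and counsellors cannot be masked to counselling, and the protocol is open about that. Classifying the outcome is a separate step that can be masked, and the protocol does not say that it is. The named adjudicators include the person who sponsors and funds the trial and the heads of the facilities where the intervention or control care is given.

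The answers themselves are also exposed. Setting a postpartum appointment is part of the intervention, and the protocol describes it as a form of behavioural contracting. A woman who agreed to a date is later asked, unmasked, whether she started a method. If misreporting or lenient classification differs between arms, it appears as a treatment effect on the primary outcome. Intention to treat and multiple imputation, the safeguards in Statistical methods (20), do not correct outcomes that are recorded wrongly.

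**Working it through.** **Step 1. Which source can show use at 14 weeks?**

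| Source | When completed | Can it show use? |
|---|---|---|
| CRF | At recruitment, in pregnancy | No |
| Appointment card | When the woman accepts a follow-up date | No; Data management (19) says it holds a proposed start date, which is intent |
| Questionnaire | 14-week visit | Yes |
| Phone call | If she is lost to follow-up | Yes |

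Only the last two can carry the endpoint. No register, dispensing record or client card is named as a check.

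**Step 2. Does the site reveal the arm?** Study setting (9) names different health centres and community units for each arm, and 16c allocates by facility. Trial design (8) instead describes randomisation of individuals. The two conflict, but staff know the arm under either because nobody is blinded. The appointment card would also give the arm away, since appointment setting belongs to the intervention.

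**Step 3. Is there room for judgement?** Outcomes (12) refers to immediate postpartum uptake, measured at or after 14 weeks. Recruitment (15) refers to a modern method, established in weeks 12 to 14. The 27% in Sample size (14) covers any method, modern or traditional. A traditional method, or a late start, could be classed either way.

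**Step 4. How large could the effect be?** The plan's own figure comes first. Six sites × 41 = 246, or 82 per arm over three arms. The printed formula with 27% v 53%, two-sided α = 0.05 and 90% power gives {1.96√(0.40×0.60×2) + 1.2816√(0.1971+0.2491)}²/0.26² = 72.5, so 73 per arm (219 in all). A continuity correction gives 81 (243), and 73/0.90 gives 82. The protocol states neither adjustment. Only the 82 per arm is used below.

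Let p be true uptake in both arms, and q₁ and q₀ the fractions of non-users counted as users in the intervention and control arms. The apparent difference is (q₁ − q₀)(1 − p). With q₀ = 0, apparent intervention uptake is p + q₁(1 − p).

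The rejection probability for a pooled two-sided z-test is Φ[(d − 1.96·s₀)/s₁] + Φ[(−d − 1.96·s₀)/s₁]. Here d is the apparent difference, s₀ the pooled and s₁ the unpooled standard error at 82 per arm. The values of q₁, and setting q₀ = 0, are assumptions. Clustering is ignored.

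| q₁ | p = 0.27: apparent uptake, gain | P(p<0.05) | p = 0.40: apparent uptake, gain | P(p<0.05) |
|---|---|---|---|---|
| 5% | 30.7%, 3.7 points | 8% | 43%, 3 points | 7% |
| 10% | 34.3%, 7.3 points | 17% | 46%, 6 points | 12% |
| 15% | 38.0%, 11.0 points | 32% | 49%, 9 points | 21% |

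Worked case, p = 0.27 and q₁ = 10%: d = 0.073, s₀ = 0.0720, s₁ = 0.0718. This gives Φ(−0.949) + Φ(−2.98) = 0.171 + 0.001 = 17%.

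In head counts, 82 × 0.73 ≈ 60 non-users are expected, so these rates mean about 3, 6 or 9 women. With 22 of 82 controls using a method, significance is first reached at 34 of 82, a gap of 12 women or 14.6 points. Producing the whole planned 26-point effect would need q₁ = 0.26/0.73 = 36%.

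**The case against.** - **Self-report.** A reader might infer that the endpoint is definitely self-reported. The protocol never says so. The questionnaire's items are not shown, the enumerator might look at a card, and 'largely' leaves room for an unnamed source. This stands: self-report is an inference from Step 1. If another source exists, it should be named.
- **Own sites.** A reader might infer that in-charges judge their own women. The text describes one joint team and no division of cases. It does not rule out own-site judging either.
- **Arm known at adjudication.** The team may already work from numbered records. That is possible, but the confidentiality section does not say that site or arm is hidden.
- **Composition.** The sub-county coordinator is not tied to one facility. The study facilities include the control centres, so their in-charges sit on the team too, and no community-unit head does. This weakens any claim that bias must favour the intervention, but it masks nobody.
- **Little discretion in a yes/no endpoint.** This is true only once the rule is fixed; Step 3 shows that the wording varies.
- **Left to a manual or SOP.** Procedures may be there. But the protocol itself fixes the team and the sources, so it should also say whether the team sees the arm.
- **The error rates.** They rest on assumed one-sided misreporting. Masked adjudication cannot correct a woman's inaccurate answer, so they do not measure its benefit. This stands in full.

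**Conclusion.** The concern holds in a limited form. The protocol assigns adjudication to trial and site staff without stating any masking, in a trial where the site reveals the arm. It names no check on what appears to be the woman's own report. Knowledge of arm can therefore influence the reporting and classification of the primary outcome. Bias toward the intervention is plausible because of the appointment commitment. It is not certain: equal misreporting in both arms adds no false difference when there is no true effect, and more in controls would reverse it.

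The size is unknown. The 8%, 17% and 32% apply only under the assumed rates of 5%, 10% and 15%, with 27% true uptake in both arms, no misreporting in controls and no clustering. They show that a few women per arm matter at this sample size, and no more. The point merits a change because the change is cheap and misclassification cannot be undone in analysis.

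**What to change.** 1. **Mask adjudication.** State that adjudicators receive records showing only the random enrolment number, with site, arm and appointment-card fields removed. They should apply one written rule for uptake (which methods count, in what time window) in all arms, and should not judge women from their own facility. A data clerk can hold the link and route the records. Because the PI also reviews the study dashboard, the PI's view of individual records should hide site and arm until adjudication is complete.
2. **Add a record check as a sensitivity analysis.** Keep the questionnaire-based outcome as primary. At the 14-week contact, copy the method and start date from the client card or, where one is kept, the facility family-planning register, identically in all arms. That such records exist is an assumption; the protocol mentions neither.

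Confirmed use should not become the main definition. The booked appointment may steer intervention women to the facility whose register is checked, while control women may more often obtain methods elsewhere. Their use would then go unconfirmed more often, which would itself favour the intervention. Report both definitions side by side.

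**Cost.** An anonymised export from the existing electronic forms and at most 246 look-ups, with no new staff. The look-ups would be made by unmasked staff, so they should copy entries and not interpret them. Masking does nothing for inaccurate answers; only the second step addresses those, and only for methods that leave a record.

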| Trial design (8) | This will be a prospective interventional study, a cluster Randomised Control Trial (RCT) conducted in Kisumu County  The study will have three arms. These will be facility intervention arm, community intervention arm and a control arm. The study will have three interacting phases. The pre-intervention phase, intervention phase and post-intervention phase. The proposed methods in each phase are not complex thus the overall design can be classified as simple intervention design.  Pre-intervention phase is for establishing sampling frame, intervention package and research tools formulation.  The aim of the intervention phase is to determine the effect of the targeted antenatal PPFP information package on the uptake of contraceptive methods during the postpartum period, in comparison with the standard of care. The intervention phase also integrates qualitative research that is aimed at identifying operational barriers and enablers of the intervention outcomes.  Randomization to control and intervention arms is at individual level within randomly selected control, community and the primary level health centres. Participants allocated to the experimental group will receive the targeted antenatal PPFP information package and those allocated to the control group will receive usual antenatal care. |
| Methods: Participants, interventions, and outcomes | |
| Study setting (9) | The study will be in Kisumu County, Kisumu East sub County. The randomly sampled facilities are Migosi Health centre and Gita Health Centre for Intervention in urban and rural area respectively. The Community Units (CU) for community-based intervention will be Kuoyo CU and Nyalunya CU in in urban and rural area respectively. The control Facility and CUs will be Kowino HC and Chiga HC and their link CUs in urban and rural area respectively. |

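### The protocol fixes the unit of allocation both as the individual woman and as the facility, which leaves the ballot's role, the intention-to-treat set and the power unsettled

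*Protocol*

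**What the plan says.** The protocol describes allocation in four places.

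- **Trial design (8)** opens with "This will be a prospective interventional study, a cluster Randomised Control Trial (RCT) conducted in Kisumu County". It sets out three arms (facility intervention, community intervention, control) and then says "Randomization to control and intervention arms is at individual level within randomly selected control, community and the primary level health centres".
- **Study setting (9)** gives each arm its own sites, one urban and one rural. On the facility intervention arm it says "The randomly sampled facilities are Migosi Health centre and Gita Health Centre for Intervention in urban and rural area respectively". Two community units are named for the community arm. Two other health centres, with their link community units, are named as control.
- **Sequence generation (16a)** says "Each client meeting the criteria will be randomly assigned to the study i.e. to the intervention and to the control arms using simple random sampling"; the draw uses a folded paper marked *yes* or *no*. It adds that intervention and control facilities are known and kept apart. **Allocation concealment mechanism (16b)** repeats this: "There will be no allocation concealment as the intervention and control facilities are known and separate to reduce contamination".
- **Implementation (16c)** says "The allocation to intervention and control is at the facility level", and then "Participants will be assigned to participate by picking a ballot paper labelled" *yes* or *no*.

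Sample size (14) gives 246 women, 41 per facility, from a comparison of 27% with 53%. Statistical methods (20a,b,c) makes the participant the unit of analysis, says the intra-cluster correlation will be accounted for without giving a value, and applies intention to treat throughout.

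**The concern.** The unit of allocation determines what may be claimed and how the data should be analysed. If women are randomised within sites, site differences are balanced between arms and a sample size for independent individuals is reasonable. If sites carry the arm, every difference between sites is also a difference between arms, and the information comes mainly from the number of sites. The protocol asserts both.

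The ballot has the same problem. In 16a it sends a woman to an arm; in 16c it decides whether she takes part. In the first case a woman who draws *no* is a control and belongs in the intention-to-treat analysis. In the second she was never in the trial. The protocol does not say which. The claim in the background section to be a rigorous randomised trial depends on the answer.

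**Working it through.** **1. The two readings side by side**

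| | Individual allocation | Facility allocation |
|---|---|---|
| Stated in | Trial design (8); 16a | 16c |
| Supported by | sample size without a design effect | cluster label in (8); separate named sites in (9); separation stated in 16a and 16b; ICC to be accounted for in (20) |
| Ballot decides | arm | participation |
| Woman who draws *no* | control, in the ITT set | not enrolled |
| Units allocated | 246 women | 6 sites, 2 per arm |

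A *yes*/*no* draw has two outcomes and the trial has three arms, so the draw alone cannot allocate. If each site belongs to one arm, no arm assignment remains to be made inside it, and the draw can only select participants. Data monitoring (21a,b) tracks acceptance among women sampled, which fits the sampling interpretation.

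The individual reading also sits badly with the equal distribution intended in Sample size (14). Suppose women in the four intervention sites were split equally by ballot while the two control sites remained control. The arms would then be 41 (facility), 41 (community) and 2 × 41 + 82 = 164 (control).

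**2. The plan's own sample size**

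Inputs from Sample size (14): p1 = 0.27, p2 = 0.53, Δ = 0.26, two-sided α = 0.05, power 90%, ratio 1. The pooled proportion is 0.40.

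Printed formula: n = [1.96 × √(2 × 0.40 × 0.60) + 1.282 × √(0.27 × 0.73 + 0.53 × 0.47)]² / 0.26² = 72.5, so 73 per arm and 219 for three arms.

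This is not 246. Two unstated steps would lead there:

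- The Fleiss continuity correction gives 81 per arm (243 in all). Rounding to two equal sites gives 82 per arm, so 246.
- A 10% dropout allowance gives 73/0.9 = 81.1, so 82 per arm.

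Neither involves clustering. Even if the whole step from 73 to 82 were read as a clustering allowance, 82/73 = 1.12, which with 41 per site corresponds to an ICC of only 0.12/40 = 0.003.

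**3. Power under each reading, one pairwise comparison, 82 per arm**

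Design effect DE = 1 + (41 − 1) × ICC; effective n = 82/DE. Power = Φ[(0.26 × √n − 1.96 × √0.48) / √0.4462]. The ICC values are assumptions, since the protocol gives none.

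| Allocation | ICC | DE | Effective n per arm | Power, normal approximation | Power, t on 2 df |
|---|---|---|---|---|---|
| Individual | n/a | 1.0 | 82.0 | 93% | n/a |
| Facility | 0.01 | 1.4 | 58.6 | 83% | 38% |
| Facility | 0.02 | 1.8 | 45.6 | 72% | 32% |
| Facility | 0.05 | 3.0 | 27.3 | 50% | 22% |
| Facility | 0.10 | 5.0 | 16.4 | 32% | 16% |

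The last column uses a t critical value with 2 degrees of freedom, because a pairwise comparison has four sites and two arms. It shows how optimistic the normal approximation is here.

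**The case against.** The best defence is that the intent is clear: a cluster trial with random sampling of women inside each site. The cluster label, the named sites, the separation stated in 16a itself and the promise to account for the ICC all point that way. This is probably what was meant, but it does not remove the sentences in (8) and 16a that place women individually into arms. A separate analysis plan could not settle the matter, because sites act on the protocol. Accounting for the ICC in the analysis also does not restore power that was not planned for.

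Five stronger readings are tempting, and the documents do not support them.

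- *That 6 × 41 = 246 proves one arm per site.* Forty-one is a site total, and the product is the same however arms are split within sites.
- *That the intention-to-treat set is itself contradictory.* The protocol never defines it in two ways; it is undetermined as a consequence of the allocation conflict.
- *That clinics would run both arms side by side, with about 20 women in each group.* 16a also says the facilities are separate, and a two-way split does not fit three arms. The realistic risk is wrong analysis and wrong reporting.
- *That sites were randomised to arms within urban and rural strata.* Study setting (9) says facilities were randomly sampled, not how sites received their arms.
- *That a specific recruitment bias can be quantified.* Absence of concealment and blinding is openly declared, but the documents give no basis for a figure.

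**Conclusion.** The point stands and needs correction. The conflict between (8) with 16a and 16c is explicit and depends on no calculation. Whether women who draw *no* count as controls is left open.

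On the facility reading the trial has two sites per arm, and random sampling of women within a site gives no protection from confounding between arms. The stated 90% power then lacks support: the normal approximation gives 83% to 32% over assumed ICCs of 0.01 to 0.10, against 93% under individual randomisation. These figures rest on the protocol's 27% and 53%, 41 women per site with none lost, and ICC values that are assumptions.

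**What to change.** Reconcile Trial design (8) and items 16a to 16c to one allocation unit. If it is the site, as the named sites indicate:

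1. Delete the individual-level randomisation sentence in (8) and the arm wording in 16a, and stop describing women as individually randomised.
2. State how the six sites got their arms, and whether the link community units count as part of the control sites.
3. Describe the ballot as random sampling of eligible women. Have the existing research assistant at each site draw from the antenatal clinic or community unit list before the study is discussed, and log draws and refusals by arm.
4. Define intention to treat as all sampled women who consent, analysed in their site's arm.
5. Restate the 90% power with a design effect over a stated ICC range, acknowledging two clusters per arm.

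The cost is rewording of the protocol and registry entry, a log, and a less favourable power figure. No extra staff are needed, since each site already has a research assistant and acceptance is already monitored. One weakness remains: the arm is known when women consent, so differential consent would be recorded but not prevented.
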